### Expected results

This study aims to evaluate an innovative and advanced scientific therapy using autologous ASCs expanding in the laboratory as an alternative to prevent limb amputation for patients with peripheral artery disease (PAD). Cellular therapy could be an alternative to improve participants’ quality of life and overall health. The study results will also evaluate clinical changes such as wound healing, quality of life, blood tests, and additional examinations. These results will provide evidence regarding the effectiveness of the proposed treatment, within the study’s established timelines. By the end of the project, we hope to develop an advanced cell therapy protocol to help in this difficult clinical situation.

### Strengths and limitations

The strong point of the study is that it is a RCT for a disease stage that has practically no solution. Through the methodology employed, it will be possible to conclude the safety and efficacy of cell therapy for PAD plus critical ischemia and ulcers.

Limitations to this study include the impossibility of performing biopsies and tracking the applied stem cells.

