### Exclusion criteria

Pregnancy planning, being pregnant, or in the postpartum period.Healed ulcer during the screening.Signs of systemic infection, active infection, devitalized tissue (necrosis) of the arterial ulcer, or infection of surgical prostheses. Participants excluded by these criteria may be reevaluated for inclusion after successful treatment with antibiotics and removal of the infectious focus (including minor amputations such as toes or forefoot).Active cancer, chemotherapy, radiotherapy, or cancer in remission for less than 6 months.Use of colchicine or immunomodulators.Infectious diseases such as Human Immunodeficiency Virus (HIV), Hepatitis B Virus (HBV), Hepatitis C Virus (HCV), and Human T-cell lymphotropic Virus (HTLV).Major amputation (at ankle, leg, or thigh level) of the limb to be studied.Diagnosed Coronavirus Disease (COVID-19) for less than 4 weeks.

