### Sample size

The sample calculation considered two independent samples with an estimated proportion of the ulcer healing rate of 75% for group 1, which will be treated with cell therapy, and 30% for group 2, which will be treated with hydrogel dressing. Assuming a test power of 80% and a significance level of 5% for a two-sided test, the sample was defined as 20 participants for group 1 and 20 participants for group 2 (1:1 allocation). This study was designed to be analyzed with intention to treat (ITT).

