### Recruitment

Participants will be recruited from June 1, 2025, to July 1, 2027. The data analysis should be finished by December 20, 2027. Eligible participants will be those who do not have an option for effective revascularization. They will be screened for inclusion in the study upon admission to the Clinical Hospital of the Faculty of Medicine, Botucatu, for treatment of peripheral artery disease (PAD) with chronic ulcers, or while receiving follow-up care at the Clinical Hospital Vascular Surgery’s Dressings Outpatient Clinic.

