### Secondary outcomes

#### 
Safety.

Death, acute myocardial infarction (AMI), cerebrovascular accident (CVA), thromboembolic events such as deep vein thrombosis (DVT) and pulmonary embolism (PE), systemic infectious condition, cancer, local infections, bleeding, worsening pain and enlargement of the ulcer area.Any adverse event not mentioned in the previous items or negative and clinically significant changes in laboratory parameters (glycemia, glycated hemoglobin, HDL, LDL, total cholesterol, triglycerides, leukogram, hematocrit, uric acid, urea, creatinine, CRP, sodium, potassium, alkaline phosphatase (ALP), alanine transaminase (ALT), aspartate transferase (AST), gamma-glutamyl transferase (GGT), bilirubin, total protein, albumin, prothrombin time (PT), partial thromboplastin time (PTT)) and tissue histological analysis.

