Follow-up of patients will continue for 120 days from the moment they receive treatment with the proposed advanced cell therapy. Time required for screening and preparations will not count toward the study follow-up period. Participants will be reassessed on days 7, 30, 60, 90, and 120 days after randomization. The closing assessment will be carried out after 120 days (assessment 6). After completing their participation in the study, the participants will be referred for routine follow-up at the vascular surgery outpatient clinic of the Clinical Hospital of the Faculty of Medicine of Botucatu. During this period, extra visits may occur, if necessary (S3 File Table 1 Assessment Schedule).

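### The protocol says the trial will be able to conclude safety, but 20 treated participants followed for 120 days cannot support that, least of all for cancer, and size and duration are not listed as limitations

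*Protocol article*

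**What the plan says.** Strengths and limitations (protocol article) presents the randomized design as the study's strong point and adds, without qualification: "Through the methodology employed, it will be possible to conclude the safety and efficacy of cell therapy for PAD plus critical ischemia and ulcers". The limitations that follow are the impossibility of biopsies and of tracking the applied cells. Nothing is said about the number treated or the time observed.

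Other sections bear on that claim:

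- **Study design** labels the trial phase I/II.
- **Sample size** sets 20 per group and rests on healing alone: "an estimated proportion of the ulcer healing rate of 75% for group 1" against 30% in the control group, with 80% power and a two-sided 5% level. No safety outcome enters the calculation.
- **Secondary outcomes, Safety** includes "systemic infectious condition, cancer, local infections, bleeding, worsening pain and enlargement of the ulcer area".
- **Exclusion criteria** rule out "Active cancer, chemotherapy, radiotherapy, or cancer in remission for less than 6 months", so people with a longer remission can enter.
- **Participant timeline** gives 120 days of follow-up from treatment, then counts the visit days from randomization. Afterwards "the participants will be referred for routine follow-up at the vascular surgery outpatient clinic" of the same hospital. The **Abstract** says monitoring lasts 90 days.
- **Recruitment** states: "Participants will be recruited from June 1, 2025, to July 1, 2027. The data analysis should be finished by December 20, 2027".

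**The concern.** Concluding that a treatment is safe means ruling out risks large enough to matter. A trial sized on a 45-point difference in healing need not be able to do that, and for uncommon or late events this one cannot. Cancer is the clearest case: it is named as a safety outcome of laboratory-expanded cells, yet the observation window is about four months.

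What is at stake is how the result will be read. The Adverse effects section treats cell-related risks as non-existent provided production is rigorous, and Data dissemination looks ahead to use in public health policy. Against that background, and with a published statement that safety can be concluded, a count of zero could be taken as confirmation when it carries little information.

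**Working it through.** **The plan's own figure.** With healing of 75% v 30%, 80% power and a two-sided 5% level, the pooled-variance formula gives

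n = [1.96·√(2·0.525·0.475) + 0.8416·√(0.75·0.25 + 0.30·0.70)]² / 0.45² = (1.384 + 0.531)² / 0.2025 = 18.1,

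so 19 per arm. The stated 20 is consistent with this. It follows from healing alone.

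**Risk of any one type of event in the treated group.** With zero events in n participants, the exact one-sided 95% upper limit is 1 − 0.05^(1/n).

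- n = 20: 1 − 0.05^(1/20) = 13.9%.
- If fewer are actually treated, the limit is higher: 15.3% for 18 and 17.1% for 16.

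The chance of seeing at least one event in 20 is 1 − (1 − p)^20: 18% for a true risk of 1%, 33% for 2% and 64% for 5%. A 5% risk would therefore go entirely unseen 36% of the time.

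**Comparison between arms.** With 20 v 20 and Fisher's exact test, 5 v 0 events are needed for p < 0.05 (p = 0.047). Power is 24% for 10% v 30% and 49% for 10% v 40%.

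**Cancer.** Person-years are 20 × days / 365.25. With zero cases, the one-sided 95% upper limit for the rate is −ln(0.05) / person-years = 2.996 / person-years.

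| Follow-up from treatment | Person-years, Group 1 | Upper limit per 100 person-years |
|---|---|---|
| 120 days (Participant timeline) | 6.6 | 46 |
| 90 days (Abstract) | 4.9 | 61 |

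The documents give no background cancer rate. Assuming 1 to 2 per 100 person-years, 6.6 person-years would yield 0.07 to 0.13 expected cases, so zero is the likely result whatever modest effect the treatment has.

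**What later records could add.** From 1 June 2025 to 1 July 2027 is 760 days, and from then to 20 December 2027 is 172 days. The figures below are potential follow-up per treated participant.

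| Assumption | Mean days | Multiple of 120 days | Person-years | Upper limit per 100 |
|---|---|---|---|---|
| Even accrual, no loss, to 20 Dec 2027: 380 + 172 | 552 | 4.6 | 30.2 | 9.9 |
| Same, less 21 days of cell expansion | 531 | 4.4 | 29.1 | 10.3 |
| Even accrual, data closed when the last participant treated reaches day 120: 380 + 120 | 500 | 4.2 | 27.4 | 10.9 |
| Later accrual, mean entry at 60% of the window: 932 − 456 − 21 | 455 | 3.8 | 24.9 | 12.0 |
| Later accrual, mean entry at 75% of the window: 932 − 570 − 21 | 341 | 2.8 | 18.7 | 16.0 |

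With even accrual, the 21-day delay and an assumed annual death or loss of 10, 20, 30 or 40%, the multiple is 4.1, 3.7, 3.3 or 3.0. Expected time for each participant is (1 − e^(−ht))/h with h = −ln(1 − annual loss), averaged over entry dates. At 40% loss that is 19.6 person-years and a limit of 15.3 per 100. Late accrual and losses together would reduce it further.

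**The case against.** The strongest reply is that this is one optimistic sentence in a paper that labels the trial phase I/II. It alters no endpoint, analysis or decision rule, and limited safety precision is normal at this stage. Cancer is one item in a long list of secondary events, and recording it is ordinary surveillance, not a promise to estimate its rate. The primary safety outcome is absence of major amputation, and the Introduction calls amputation and death rates high, so a zero count is least likely there. All of this stands, and it limits the point to what may be claimed. It does not rescue the sentence, which is unqualified and whose accompanying limitations omit size and duration.

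A reader might also infer that nothing is recorded after the last visit and that later cancers would be ignored. The article does not say so. It says only that participants are referred to routine care, and the statistics section mentions long-term clinical analyses by Kaplan-Meier. The assessment schedule, consent form and full protocol are supplements that are not shown, and later safety follow-up may be planned there.

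A second tempting reading is that the trial's own calendar offers more than four times the observation time. That holds only for even accrual, almost no deaths or losses, complete charts and a late data cut. The article gives no accrual pattern or death rate. Nor would the extra time cure the problem: the limit for cancer would still be about 10 to 16 per 100 person-years, and the 13.9% limit depends on 20 participants and would not move.

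**Conclusion.** The point holds as a criticism of the stated claim. The design cannot deliver a conclusion on safety: zero events of a type among 20 treated participants leaves risks up to 13.9% open, and zero cancers excludes only rates above about 46 per 100 person-years at 120 days, or about 61 at 90 days. The 13.9% assumes that all 20 are treated and observed; the rates assume full follow-up of all 20. Any shortfall makes both worse.

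The exposure figures rest on a follow-up length on which the Abstract and Participant timeline disagree. If the visits are counted from randomization, and randomization coincides with tissue collection, 14 to 21 days of cell expansion would leave Group 1 only 99 to 106 days after treatment at the day-120 visit.

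The documents do not support saying that the trial is unsafe, that later records will be discarded, or that a longer window would make a cancer conclusion possible. The point does not block the trial, but the wording should be corrected before results are interpreted against it.

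**What to change.** **Wording, in Strengths and limitations.** Replace the safety part of the claim with text such as: *The trial will give preliminary, descriptive safety data over the stated follow-up in 20 treated participants. Zero events of a given type does not exclude a risk below about 14%, and no conclusion on cancer can be drawn.* List sample size and duration of follow-up as limitations.

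**Follow-up.** Reconcile the 90 days in the Abstract with the 120 days in Participant timeline, and state whether the visit days count from treatment or from randomization.

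**Optional supplement.** If the full protocol does not already plan it and consent allows, add to Secondary outcomes and Participant timeline one record check of both groups for new or recurrent cancer and for death. Use a common cut-off before the analysis, exclude those who withdrew consent, and report it descriptively with person-time and exact limits. Expect roughly three to four times the observation time, depending on accrual, deaths and losses: about 19 to 30 person-years in Group 1, with zero cases excluding only rates above about 10 to 16 per 100.

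**Cost.** The rewording costs nothing beyond a more modest claim. The record check means one chart review of up to 40 participants at the same hospital, with no extra visit or test. It may need consent wording for record access after the last visit, and it would miss some care given elsewhere.

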### Ethical and regulatory considerations

The protocol, ICF, investigator’s brochure, and other pertinent documents were submitted and approved by the Plataforma Brasil system (https://plataformabrasil.saude.gov.br), the CEP/CONEP under the CAAE protocol 39873320.3.0000.5411, version 4, approved in 02/29/2024.(S4 File Protocolo Stem Cell in Portuguese and English)

Participants will be invited to join the study by a physician who is part of the study team, and they will sign an ICF (S2 File ICF in Portuguese and English). Each participant or their legal representative must complete two copies of the ICF, which will be dated and signed after all doubts have been clarified. Both copies will also require the signature of a witness and the researcher responsible for the RCT. One signed copy will be given to the participant, while the other will be securely archived in both physical and digital formats for a period of 10 years. Participants have the right to withdraw their consent to participate in the RCT at any time without facing any harm or embarrassment. There will be no form of remuneration provided to the participants. However, all care provided to participants during the study will be covered by the study sponsor.

Furthermore, the study will be conducted according to the approved protocol and applicable national and international ethical guidelines:

Good Clinical Practice GuidelinesGood Laboratory Practice GuidelinesWorld Medical Association (WMA) Declaration of Helsinki

Any change to the protocol, consent form, or brochure will be sent to the Brazilian ethical and regulatory systems in the form of an amendment before being implemented in the study, except in cases where it is necessary to eliminate an immediate risk to participants.

### Data dissemination

The findings from this RCT, which investigates the safety and efficacy of utilizing adipose-derived stem cells (ASCs) for treating wounds in patients suffering from CLI and ischemic ulcers without a good option for treatment, will be published in peer-reviewed, open-access scientific journals. Furthermore, these results will be showcased at national and international scientific conferences and shared with the public to raise awareness. Participants will receive updates on their treatment outcomes in a comprehensive medical report at their final follow-up assessment. We prioritize protecting sensitive information; therefore, participants’ identities will remain confidential, and no identifying images will be disclosed. This study not only aims at the advance of cell therapy but also aspires to pave the way for broader clinical applications in treating CLI. In Brazil, we foresee a future where cell therapy is integrated into public health policies, supported by the Unified Health System (SUS). We are committed to ensuring that the results of this study are reliable and accessible to both the scientific community and the public. Our outreach efforts to disseminate and promote these findings will span a minimum of five years, with the potential to influence the scientific community and the broader public health landscape.

### Conclusion

This protocol describes in detail the planning and execution of the clinical trial aimed at offering an alternative clinical treatment for patients in an advanced stage of PAD who present critical ischemia of the lower limbs (CLI) and arterial ulcers who exhausted all possibilities of revascularization. Therefore, these are patients who have a high probability of limb amputation, and the proposed cell therapy may bring benefits. Few clinical studies with advanced cell therapy have been carried out in Brazil and only recently have we had a clearer regulatory framework in this regard. The results of this clinical trial have the potential to increase the range of treatments for patients with PAD and CLI. The findings could influence future research and clinical practices, promoting significant advances in cell therapy.
